##### Aim 3 (exploratory)

Finally, we will examine the association between practice-related brain activation changes in the cognitive control and reward networks and individual differences (e.g., dependence, motivation, gender, self-report measures of impulsivity, and behavioral measures of cognitive control). We will perform Pearson correlation analyses to examine the relationship between dlPFC brain activation changes (i.e., the percentage signal change in response to negative smoke compared to positive smoke conditions from pre- to post-treatment) and motivation to quit smoking, nicotine dependence, personality and psychological variables, and cognitive performance. In addition, we will use *t*-tests to examine gender differences in brain activation changes. Finally, we will use multiple regression to explore the effects of gender, marijuana use, motivation to quit smoking, dependence, self-report measures of impulsivity, and behavioral measures of executive function, decision-making, inhibition, and demand on changes in cognitive control.

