#### Other objectives

Additional objectives are to examine the association between practice-related brain activation changes in the cognitive control network and individual differences (e.g., nicotine dependence, motivation, and sex). We hypothesize that practice-related increases in brain activation in the cognitive control network are expected to be greatest among more dependent and less motivated smokers as well as women.

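### Exploratory Aim 3 hypothesises who gains most from practice, but none of its named tests contains group or a group × characteristic term

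*Protocol article*

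**What the plan says.** Other objectives gives a directional hypothesis: gains attributable to practice are "expected to be greatest among more dependent and less motivated smokers as well as women".

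The section Aim 3 (exploratory) keeps the same subject: "we will examine the association between practice-related brain activation changes in the cognitive control and reward networks and individual differences". It then names three procedures.

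- Correlations: "We will perform Pearson correlation analyses to examine the relationship between dlPFC brain activation changes" and motivation, dependence, personality and psychological variables, and cognitive performance.
- t-tests "to examine gender differences in brain activation changes".
- A regression: "we will use multiple regression to explore the effects of gender, marijuana use, motivation to quit smoking, dependence, self-report measures of impulsivity", followed by behavioural measures.

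Group is in none of the three, and the set of participants to be analysed is not named. The article is explicit on both matters elsewhere: Aim 1 is tested through a group × time interaction, and Aim 2 is confined to the practice arm. The opening of the Analysis plan words Aim 3 more loosely, as exploring effects of individual differences on activation change.

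**The concern.** A practice-related increase is the part of the pre-to-post change that practice causes. Asking in whom it is greatest means asking whether the difference between arms varies with the characteristic. A correlation of change with dependence does not measure that. In the practice arm alone, nothing shows what the correlation would have been without practice. Pooled without a group term, the test averages the two arms' associations, so control participants are included but do not serve as a comparator.

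Change that varies with a characteristic but not because of practice is possible in this design. Everyone receives the brief counselling (Pre-treatment scan appointment), the control log asks about use of coping techniques (No practice group), and everyone is scanned twice on the same task. Power and sample size assumes zero mean change in controls. That concerns the average and does not exclude change that varies with dependence, motivation or sex.

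At stake is the interpretation of Aim 3. A characteristic that merely accompanies change could be read as marking who responds to practice, and a real modifier could be hidden by pooling. The Aim 1 test is unaffected.

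**Working it through.** **The plan's own figure.** The article states no power for Aim 3. Its Aim 1 figure reproduces: d = 0.0991/0.1415 = 0.70, 40 per group, two-sided α = 0.025. The noncentrality is 0.70 × √(40/2) = 3.13 on 78 df, giving 79.9% against the stated 79%.

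**Inputs for Aim 3.** From the article: 40 per arm, and an expected 1:1 gender ratio, hence about 20 women and 20 men per arm. Assumed: the correlation r between characteristic and change, two-sided α = 0.05, normal data, both scans available for all 80, and a 0.70 SD mean difference in change between arms.

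**Tests compared.**

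- Practice arm: t = r√(n−2)/√(1−r²), n = 40.
- Pooled: the same formula, n = 80, no group term.
- Interaction: difference between the two within-arm slopes divided by its standard error, 76 df.

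**Same r in both arms, so practice modifies nothing.** Rejection rates by simulation (10,000 trials per row or more):

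| r in both arms | Practice arm | Pooled | Interaction |
|---|---|---|---|
| 0.05 | 6% | 7% | 5% |
| 0.1 | 9% | 13–14% | 5% |
| 0.2 | 23% | 38% | 5% |
| 0.3 | 48% | 73% | 5% |
| 0.4 | 74% | 94% | 5% |

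The pooled entry at r = 0.1 is 13% with the 0.70 SD difference between arms and 14% without it.

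Hand check at r = 0.3 with Fisher's z. Practice arm: atanh(0.3) × √37 = 0.3095 × 6.083 = 1.88, so power ≈ Φ(1.88 − 1.96) = 47%. Pooled: the difference between arms shrinks r to 0.3/√(1 + 0.70²/4) = 0.283, and atanh(0.283) × √77 = 2.55 gives Φ(2.55 − 1.96) ≈ 72%.

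**Gender t-test, same 0.5 SD difference in both arms.** Practice arm, 20 v 20: noncentrality 0.5 × √(20/2) = 1.58, rejection 34%. Pooled, 40 v 40: 0.5 × √(40/2) = 2.24, rejection 60%. The interaction test stays at 5%.

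**Pooling can also hide modification.** With r = +0.3 under practice and −0.3 without, the pooled test rejects in 6% of trials and the interaction in 76%.

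**What the interaction can detect.** With r = 0.3, 0.4 or 0.5 in the practice arm and 0 in controls, its power is 27%, 44% and 63%. For a gender × group difference of 0.5 SD, the standard error is √(4/20) = 0.447 SD, the noncentrality 0.5/0.447 = 1.12 and the power 20%; for 0.8 SD it is 42%.

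**The case against.** The strongest reply is that the tests suit the aim as the Analysis plan words it. They examine associations with change, the aim is labelled exploratory, and neither the sample size nor the primary test rests on it. A condensed article may also leave covariates and interaction terms to an analysis plan that is not shown. Part of this stands: the stakes are limited, and an unshown plan may add the term. But the article itself chose and listed the tests, and the directional hypothesis under Other objectives has no test among them that matches it.

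Three stronger readings are tempting, and the document does not support them.

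- A reader might infer that regression to the mean alone would create a sizeable spurious correlation. If a characteristic correlates q₁ with the pre contrast and q₂ with the post contrast, with equal variances and pre-post correlation ρ, its correlation with change is (q₂ − q₁)/√(2(1−ρ)). With ρ = q₁ = 0.5 this is −0.25 only if q₂ = ρq₁ = 0.25, that is, if the characteristic relates to the post value only through baseline. A stable trait such as sex has q₂ = q₁ when nothing changes, which gives zero.
- A reader might take the rejection rates as the trial's false-positive rates. They are the power to detect an association that was assumed; no such association is documented. Different, counterbalanced stimulus sets at the two scans also give some protection against habituation, and habituation would matter only if it varied with the characteristic.
- A reader might conclude that the multiple regression should be abandoned. It explores factors outside the three hypotheses, including marijuana use, a stratification factor, and can stay as description.

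**Conclusion.** The point holds as a mismatch between a stated hypothesis and the tests named for it. Followed as written, the Aim 3 analyses cannot show that dependence, motivation or sex modifies the effect of practice, under either reading of the analysis set. This conclusion needs no numerical assumption.

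The size does. If the correlation without practice is near zero, little is lost: about 6–7% rejection at r = 0.05. At r = 0.2 to 0.4 shared by both arms, a test without a group term rejects in 23% to 94% of trials when practice modifies nothing. The article does not say where in that range the truth lies.

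The correction should be made, but its weight is moderate, because the aim is exploratory and Aim 1 is untouched.

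**What to change.** For each characteristic in the hypothesis (dependence, motivation, sex), use all randomised participants and fit:

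post contrast = β₀ + β₁·baseline contrast + β₂·group + β₃·characteristic + β₄·(group × characteristic) + error

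Report β₄ with its confidence interval as the result for the Other objectives hypothesis. Modelling dlPFC change on group, characteristic and their interaction is acceptable; adjusting the post contrast for baseline is preferred. Keep the planned correlations, t-tests and multiple regression, labelled as descriptive correlates of change, and state which participants each uses.

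The cost is wording and a few extra model fits; no new data or visits are needed. The downside is precision: at N = 80 the interaction has low power for moderate effects, so present it as an exploratory estimate, and do not read a non-significant result as absence of modification. If the interaction is not wanted, the alternative is to reword the hypothesis as one about correlates of change.

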#### Power and sample size

The sample size was based on aim 1 and calculated based on changes in brain activation observed in pilot data following 1 week of practicing CBT skills and 2 weeks of CBT sessions. Assuming the no practice group will have a mean of 0 change in brain activation between day 7 and day 21, and equal variance in the two groups, our preliminary data suggest Cohen’s *d* effect sizes of 2.77 and 3.70 for dlPFC and vmPFC, respectively. These effect sizes suggest *n* = 5 and 4 subjects per group are required to achieve 80% power at 0.05/2 = 0.025 significance level (Bonferroni correction needed to compensate for tests involving each of two brain regions) in a two-sided two-sample *t*-test. However, the small sample in our pilot data (*N* = 6) also indicates wide 95% confidence intervals. Using the conservative estimates of the lower bound of the mean and upper bound of the standard deviation, the effect sizes are (0.0991/0.1415) = 0.70 and (0.2037/0.1889) = 1.08. Using a sample size of *n* = 40 per group provides 79% and > 99% power for dlPFC and vmPFC, respectively; the power will be greater if the actual effect sizes are larger than the conservative estimates.

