### Study objectives

#### Primary objective

The primary objective is to identify the impact of practicing compared to not practicing delaying smoking on functional brain activation changes in the cognitive control networks in response to smoking cues. We hypothesize that practice vs. no practice will lead to greater brain activation increases in the cognitive control network when comparing pre- to post-intervention.

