##### Regulation-of-craving task data preprocessing

The fMRI images will be realigned to the third slice collected in each scanning session to correct for motion. The images will be spatially smoothed with a 4-mm full width at half maximum (FWHM) Gaussian blur. Timepoints during which participants move more than 0.3 mm within a TR will be censored. Functional and anatomic images obtained within each session will be aligned and normalized to Talairach and Tournoux’s [35] stereotaxic atlas. Regressors representing the experimental conditions of interest (i.e., positive smoke, negative smoke, positive food, and negative food) will be modeled with a block response function and entered into the multiple-regression analysis using a random-effects model. Motion parameters will be included as nuisance regressors.

The primary contrast of interest will be negative smoke minus positive smoke, which represents an analog of the exertion of cognitive control minus general brain activation engendered by attending to smoking cues. The primary outcome analysis will focus on the a priori ROI, the dlPFC. In addition, an exploratory whole-brain analysis will be used to identify regions outside the dlPFC cognitive control network that may change with practice (e.g., the insula). The dlPFC ROI has been selected based on previous studies [5, 23, 24, 36]. The dlPFC will be defined using anatomical masks for the dlPFC based on the superior frontal gyrus and the middle frontal gyrus regions identified by AFNI’s whereami function. Multiple comparisons will be corrected using a familywise approach in which clusters will be considered significant at *p*_voxelwise_ < .01 and *p*_corrected_ < .05 within the dlPFC for the ROI analysis and within the whole-brain for the exploratory whole-brain analysis. The minimum cluster size will be determined using AFNI’s 3dClustSim function. The spatial autocorrelation function (acf) option was used in AFNI’s 3dFWHMx to estimate intrinsic smoothness and 3dClustSim to estimate the probability of false positives [37, 38]. The mean percentage signal change from dlPFC clusters that pass cluster thresholding will be used as the primary outcome data to test the hypothesis described in aim 1.

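### The power section sizes aim 1 as two Bonferroni-corrected tests (dlPFC and vmPFC at 0.025), but the analysis plan has one primary region, the dlPFC, so the stated power and level do not describe the planned test

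*Protocol article*

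**What the plan says.** All places are in the protocol article.

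- **Power and sample size.** The calculation is tied to aim 1. It uses a "0.05/2 = 0.025 significance level", justified as a "Bonferroni correction needed to compensate for tests involving each of two brain regions", "in a two-sided two-sample *t*-test". It starts from pilot "effect sizes of 2.77 and 3.70 for dlPFC and vmPFC, respectively" and moves to conservative values: "the effect sizes are (0.0991/0.1415) = 0.70 and (0.2037/0.1889) = 1.08". With 40 per group it reports 79% power for dlPFC and more than 99% for vmPFC.
- **Aim 1.** The percentage signal change for the negative-smoke versus positive-smoke contrast is computed for one a priori region, the dlPFC. It is tested through the group × time interaction. No significance level is attached.
- **Regulation-of-craving task data preprocessing.** "The primary outcome analysis will focus on the a priori ROI, the dlPFC". An anatomical mask is defined for the dlPFC only. The .05 given here is a cluster-corrected imaging threshold. A whole-brain analysis is labelled exploratory.
- **Primary objective.** This concerns "functional brain activation changes in the cognitive control networks in response to smoking cues". It names no region of interest.
- **Background.** vmPFC is listed under the reward network and dlPFC under the cognitive control network.
- **Aim 3 (exploratory).** The opening sentence refers to "practice-related brain activation changes in the cognitive control and reward networks and individual differences". The correlations then specified use dlPFC change.

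**The concern.** The two sections describe different primary test families. The power section counts two confirmatory tests and pays for them by halving alpha. The analysis sections contain one. After the Background, vmPFC is named only in the power section: it has no mask, no hypothesised direction and no named test. The reward network returns only in exploratory aim 3, and the vmPFC is otherwise reached only anatomically, by the exploratory whole-brain analysis.

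Two things follow. First, the quoted power does not belong to the planned test. The >99% belongs to a comparison that aim 1 does not make, and the 79% is computed at a level whose only stated reason is that comparison. Second, 0.025 is the only level tied to aim 1, yet aim 1 as written gives no reason for it. A dlPFC p-value between 0.025 and 0.05 would miss the level in the power section, but could be presented as positive on the ground that there is only one primary region. The vmPFC could likewise be presented afterwards as a powered co-primary region or as exploratory.

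**Working it through.** **Inputs (Power and sample size):** 40 per group; two-sided two-sample t-test; alpha 0.05/2 = 0.025; d = 0.0991/0.1415 = 0.70 (dlPFC) and 0.2037/0.1889 = 1.08 (vmPFC); pilot d = 2.77 and 3.70. **Assumption:** the level for a single primary test would be 0.05, the figure that the document divides by 2.

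**Method.** With two time points, the group × time interaction is equivalent to a two-sample t-test on the change score. Power comes from the noncentral t distribution with df = 2n − 2 and noncentrality d·√(n/2). It is the probability that |t| exceeds the critical value t(1 − α/2, df).

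**Step 1: reproduce the plan's figures at 0.025.** For n = 40, df = 78 and the critical value is 2.285.

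| Case | Noncentrality | Recomputed | Stated |
|---|---|---|---|
| dlPFC, d = 0.70 | 0.70 × √20 = 3.130 | 79.9% | 79% |
| vmPFC, d = 1.08 | 1.08 × √20 = 4.830 | 99.4% | >99% |
| Pilot dlPFC, d = 2.77 | 2.77 × √(5/2) = 4.380 | n = 5 (92.1%; n = 4 gives 79.5%) | n = 5 |
| Pilot vmPFC, d = 3.70 | 3.70 × √(4/2) = 5.233 | n = 4 (96.4%; n = 3 gives 79.1%) | n = 4 |

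The printed figures reproduce, the 79% to within one percentage point. They do rest on the two-region split.

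**Step 2: the single dlPFC test, n = 40 per arm, d = 0.70.**

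| Two-sided level | Critical value | Power | d detectable with 80% power |
|---|---|---|---|
| 0.025 | 2.285 | 79.9% | 0.70 |
| 0.05 | 1.991 | 87.1% | 0.63 |

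**Step 3: the unclear band.** The chance that p falls between 0.025 and 0.05 is essentially the difference between the two powers.

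- d = 0.70: 87.1% − 79.9% = 7.2%
- d = 0.60: 75.5% − 65.5% = 10.0%
- d = 0.50: 59.8% − 48.4% = 11.4%

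**Step 4: sample size for 80% power at d = 0.70.** About 33 to 34 per group at 0.05 (33 gives 79.97%, 34 gives 81.2%), and about 41 per group at 0.025 (40 gives 79.9%). The planned 40 exceeds the first and is one short of the second.

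**The case against.** Four points on the other side carry weight.

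- **Nothing is miscalculated, and the mismatch is on the safe side.** This stands. If only the dlPFC is tested, power is at least what is stated. If 0.025 is kept, type I error is not inflated. A reader might infer that the trial is underpowered or its error rate uncontrolled; the figures support neither.
- **The document does not state two rival levels for the aim 1 test.** This also stands. A reader might infer that the single-region plan sets 0.05, so that the decision rule is wholly undetermined. Aim 1 gives no level, and the .05 in the preprocessing section is a cluster threshold applied before the mean signal change enters the ANOVA. What remains is one stated level whose rationale aim 1 does not support.
- **vmPFC is not wholly absent from the analyses.** This stands in part. A reader might infer that it is never examined, or that aim 3 is confined to the dlPFC. Aim 3 mentions reward networks, its gender comparison is not restricted to the dlPFC, and the whole-brain analysis covers the vmPFC. None of these is a named or confirmatory vmPFC test. Nor does the primary objective itself fix a single region: it names a network, which excludes the reward network but does not single out the dlPFC.
- **Moving to 0.05 would relax the only stated level while the trial is recruiting.** This is fair, and the fix therefore also offers keeping 0.025 for the dlPFC alone.

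The inconsistency survives all four. It is not detail left to an analysis plan: any such plan would have to depart from either the two-region family or the single primary region.

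**Conclusion.** The point holds as an internal inconsistency that should be fixed. The power section describes a two-region primary family at 0.025; aim 1 and the primary outcome definition describe one region. The stated 79% and >99% are correct for the former and do not describe the latter. The practical size is about 7 percentage points of power at d = 0.70 (79.9% against 87.1%), with a 7% to 11% chance, for true effects between 0.70 and 0.50, of a dlPFC p-value whose status is unclear. On this point neither the sample size nor error control is at risk.

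The recomputed power assumes 40 evaluable participants per arm, as the document's own figure does; that is all 80 randomised, with no allowance for loss in the calculation. It also treats the outcome as a fixed regional mean. The preprocessing section takes the mean from dlPFC clusters that pass thresholding, so 87% and 80% are comparable with the document's 79% but are not a full description of that outcome.

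**What to change.** State the primary family and its level in the same words in aim 1 and in the power section, before outcome data are analysed. Two options are coherent:

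- **(a) dlPFC as the sole primary test.** Either at two-sided 0.05, with power restated as about 87% at d = 0.70 with 40 evaluable per arm; or at 0.025, if the sponsor prefers not to relax the stated level mid-trial, with power of about 80% and the two-region reason replaced. In both cases remove the vmPFC power figure and label vmPFC exploratory.
- **(b) dlPFC and vmPFC as co-primary.** Name vmPFC in aim 1, define its mask and hypothesised direction, and test each region at 0.025. The existing power figures then stand, and the primary objective and primary outcome definition must be widened to cover the reward network.

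The cost is wording in the protocol or SAP. No new participants, data or procedures are needed. Option (b) changes the primary objective, so it would need a formal amendment under the article's Modifications of the protocol section.

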## Methods/design

### Study overview

We will use a randomized design (parallel group, two-arm, superiority trial with a 1:1 allocation ratio) to examine the impact of practicing delaying the first cigarette of the day on cognitive control brain networks during an fMRI cue-reactivity task (see Fig. 1). Smokers (*N* = 80) will receive tips on how to resist the urge and control cravings to smoke and then be randomized either to practice progressively delaying their first cigarette of the day over a 2-week period (practice) or not to practice delaying their first cigarette and smoke as usual over a 2-week period (no practice). Portable carbon monoxide (CO) monitors will be used to assess objectively the timing of the first and second cigarettes of the day (days 1–7) and subsequently to monitor practice adherence (i.e., the delay of the first cigarette of the day; days 8–21). All participants will be given brief advice on techniques to help them control urges to smoke based on cognitive behavioral therapy (CBT) techniques. Participants will continue monitoring their smoking behavior regardless of group assignment. At baseline (day 7) and following 2 weeks of practice (day 21), participants in both arms will complete an fMRI session during which they view smoking and food cues and are asked to rate how much they want them. All study procedures will be conducted in accordance with the Code of Ethics of the World Medical Association (Declaration of Helsinki) and have been approved by the Institutional Review Board of the University of Kansas (protocol STUDY00004095). This experiment is registered at ClinicalTrials.gov (NCT03080844).

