### Data management

Study data will be collected and managed using REDCap (Research Electronic Data Capture), which is hosted at the University of Kansas Medical Center [63]. REDCap is a secure web-based application designed to support data capture for research studies. It provides: (1) an intuitive interface for validated data entry, (2) an audit trail for tracking data manipulation and export procedures, (3) automated export procedures for seamless data downloads to common statistical packages, and (4) procedures for importing data from external sources. All self-report data will be entered directly into REDCap by participants and all daily monitoring logs will be double entered. Physical documents will be kept in a locked cabinet accessible only by study staff to comply with confidentiality requirements. MRI data will be sent directly from the scanner to the Hoglund Brain Imaging Center server, which runs XNAT 1.6.4 [64], an open-source imaging informatics platform designed to facilitate management of imaging. Task and resting state fMRI data will be checked by trained research personnel to ensure the quality of acquired and preprocessed data prior to group analysis. As a relatively short-term study with minimal participant risks, a data monitoring committee will not be used. Any adverse events (although these are anticipated to be minimal) will be reported to the local institutional review board as per local standards. The trial will be subject to random auditing per local standards but no auditing by within-study staff is planned.

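### The power statement counts all 80 randomised smokers as analysable; on its own inputs, losing 5 to 20% of scan pairs would lower the 79% dlPFC power to about 78 to 69%

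*Protocol article*

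**What the plan says.** The Study overview describes a "parallel group, two-arm, superiority trial with a 1:1 allocation ratio" and attaches the sample size to randomisation: "Smokers (*N* = 80) will receive tips on how to resist the urge and control cravings to smoke and then be randomized". The Abstract does the same. Randomisation takes place at the day 7 visit, after the baseline scan and the brief counselling (Randomization and blinding).

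Power and sample size assumes a "two-sided two-sample" *t*-test comparing the arms on change between days 7 and 21, at a "0.05/2 = 0.025 significance level (Bonferroni correction needed to compensate for tests involving each of two brain regions". From pilot bounds that it calls conservative, "the effect sizes are (0.0991/0.1415) = 0.70 and (0.2037/0.1889) = 1.08" for dlPFC and vmPFC. It concludes that "40 per group provides 79" per cent power for the dlPFC and more than 99% for the vmPFC. The one qualification is favourable: power rises if the true effects are larger.

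Aim 1 needs a dlPFC value for each participant at both time points. Data management adds a check before group analysis: "Task and resting state fMRI data will be checked by trained research personnel to ensure the quality of acquired and preprocessed data". Payments to encourage retention are described at the consent visit and at both scan visits. No expected loss is given. Aim 1 and the task preprocessing section name one primary region, the dlPFC.

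**The concern.** The number randomised and the number analysed are different quantities, yet the protocol prints the same value for both. Two weeks of intervention and a second MRI visit lie between them, and scan quality is then checked. In a *t*-test on change, a participant without two usable scans contributes nothing.

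At stake is how the 79% is read. It is the power with no loss at the assumed effect size, and a reader would naturally take it as the power expected from randomising 80 people. Any lost pair lowers it on the stated inputs, and the section does not say so.

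**Working it through.** **Inputs, from Power and sample size unless noted**
- Randomised: 80 at 1:1, so 40 per arm (Study overview).
- Analysed in the power calculation: 40 per arm.
- dlPFC effect size: 0.0991/0.1415 = 0.70.
- vmPFC effect size: 0.2037/0.1889 = 1.08.
- Two-sided alpha: 0.05/2 = 0.025.
- Loss of scan pairs: not stated. I assume 5, 10, 15 and 20%, equal in both arms.

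**Formula.** For *n* complete pairs per arm, df = 2*n* − 2 and the noncentrality parameter is d√(*n*/2). Power is the probability that a noncentral *t* variable with these parameters falls beyond ± the two-sided critical value.

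**Reproducing the plan's figure.** With *n* = 40, df = 78, the noncentrality is 0.70 × √20 = 3.130 and the critical value at 0.025 is 2.285. Power is 79.9%, against a stated 79%. For the vmPFC the noncentrality is 1.08 × √20 = 4.830 and power is 99.4%, against a stated value above 99%. Both figures reproduce.

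**dlPFC power when pairs are lost (d = 0.70)**

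| Assumed loss | Pairs per arm | Noncentrality | Power at 0.025 | Power at 0.05 |
|---|---|---|---|---|
| 0% | 40 | 3.130 | 79.9% | 87.1% |
| 5% | 38 | 3.051 | 77.6% | 85.4% |
| 10% | 36 | 2.970 | 75.0% | 83.4% |
| 15% | 34 | 2.886 | 72.2% | 81.2% |
| 20% | 32 | 2.800 | 69.2% | 78.7% |

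At 0.025, a 10% loss costs 79.9 − 75.0 = 4.9 points and a 20% loss costs 79.9 − 69.2 = 10.7 points. One lost pair per arm (39 per arm) leaves 78.8%. The vmPFC is hardly affected: 97.7% with 32 per arm.

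**Why the last column is relevant.** The 0.025 level is justified by testing two regions, but Aim 1 and the task preprocessing section make the dlPFC the only primary region. If that is the intended analysis, 0.05 is the matching level and the design has room for loss. If two regions are to be tested, 0.025 stands and there is almost none.

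**The case against.** **No loss rate is given.** A reader might infer that the trial does not deliver its stated power. The documents do not support that. The 79% reproduces at 40 per arm, and any shortfall depends on a rate the protocol does not state.

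**The effect size is a cautious bound.** This stands. The 0.70 pairs the lower bound of the mean with the upper bound of the standard deviation, and the pilot point estimate is 2.77. At 0.025, an effect of 0.80 gives 81% power even with 32 per arm. So 79% is not a ceiling on the trial's power. It is, however, the figure the plan chose to print, and that figure should match the number analysed.

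**The routes to loss are narrow.** This partly stands. The 0.3 mm rule censors time points and does not remove scans or participants. The quality check has no stated exclusion rule. Those who drop out before day 7 are never randomised, and entrants must be willing to attend all visits. What remains is a missed day 21 scan or a scan judged unusable. It is also too strict to say that all 80 are needed, since 78 complete pairs still give 78.8%.

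**The article condenses a fuller protocol.** An expected attrition figure could sit there. But an allowance would make the number randomised exceed twice the number analysed, and the article prints the two as equal. A fuller document with an allowance would therefore conflict with one of these printed figures.

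**The 80% target is missed.** A reader might infer this from 79%. The section attaches 80% only to the pilot-based sizes of 5 and 4 per group, and the computed value at 40 per arm is 79.9%.

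**Conclusion.** The point holds as a matter of what the 79% refers to. The calculation is correct, but it describes 40 complete scan pairs per arm, while 40 is the number randomised per arm. At d = 0.70 and two-sided alpha 0.025, dlPFC power would be about 78, 75, 72 or 69% with 5, 10, 15 or 20% of pairs lost. These values rest on the assumed loss range, equal loss in the two arms, and the plan's own effect size and test.

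The sensitivity comes largely from the 0.025 level. At two-sided 0.05 for the single primary region, power stays at about 79% or more up to 20% loss. This calls for a corrected statement of power; it does not show that the trial is too small.

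**What to change.** Keep N = 80 and make two changes to Power and sample size.

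1. State that 80 is the number randomised, give the expected number of evaluable pairs with its basis, and restate dlPFC power on that number. Illustrative wording, if 15% loss were expected: *Eighty smokers will be randomised. With 34 evaluable pairs per arm, power for the dlPFC is 72% at d = 0.70 and two-sided alpha 0.025.*
2. Reconcile the two-region 0.025 level with the single primary dlPFC region in Aim 1 and the preprocessing section, and quote power at the level that will be used. At two-sided 0.05 the figures are 87% with 40 per arm, 81% with 34 and 79% with 32.

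The cost is one or two sentences and no extra recruitment. If 0.025 is kept, the stated power is somewhat less favourable.
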